### Follow up

Pregnant women will undergo an ultrasound at 7 and 11 weeks of gestation to classify the pregnancy as clinical or ongoing singleton or multiple pregnancy.

Women will be contacted by telephone to enquire on the pregnancy, delivery and the health of the child. Detailed information on maternal complication will be obtained from the obstetrician treating the woman concerned. The focus will be on gestational diabetes and hypertensive disorders. When necessary, child health centres and/or paediatricians will then be contacted for specific information. Certainly not all couples will complete the 8 months of treatment. Drop-outs will largely represent normal patient flow. We aim to keep track of all drop-outs and to document the reason for the drop-out in the database.

A structured case record form (CRF) is used to register reproductive outcome, fertility treatments as well as the course and outcome of subsequent pregnancies.

### Withdrawal of individual patients

Women can leave the study at any time for any reason if they wish to do so. Women who drop out of the study will be asked to provide the reason for dropping out. This reason will be recorded. Women who drop out of the study will be treated according to the local protocols and guidelines.

### Outcome measures

#### Primary outcome measure

The main primary outcome measure will be birth of a healthy child resulting from a pregnancy that was established in the first eight months after randomisation. A live birth is defined as any ongoing pregnancy with a gestation time beyond 24 weeks. After randomisation women will receive a maximum of six treatment cycles.

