## Objective

Our primary objective is to evaluate four treatment regimens in women with WHO type II anovulation that failed to conceive after six ovulatory cycles with CC in terms of singleton live birth. Secondary objectives are to assess the safety and cost-effectiveness for these treatment regimens and to optimise guideline recommendations.

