#### Secondary outcome measures

• Multiple pregnancy, defined as a registered heart beat of at least two fetuses at 12 weeks of gestation.

• Clinical pregnancy, defined as any registered heart beat at sonography.

• Miscarriage, defined as loss of an intra uterine pregnancy (confirmed by ultrasound or histological examination) before the 20th week of pregnancy.

• Ovulation rates, assessed by a biphasic basal temperature curve, midluteal progesterone (> 16 nmol/l), detection of LH surge or sonography.

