#### Economic evaluation

The economic evaluation will be performed alongside the clinical trial. The economic evaluation will be designed as a cost-effectiveness analysis of the addition of IUI, use of gonadotrophins or the combination of both as compared to CC alone, with the costs per singleton pregnancy within eight months after randomisation resulting in live birth as the primary outcome measure. We will also assess the time to a successful pregnancy in the cost-effectiveness analysis. In this analysis, costs and effects will be discounted for 4% per year.

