### Power calculation

The analysis will be by intention to treat. Two comparisons will be made, one in which CC is compared to gonadotrophins and one in which the addition of IUI is compared to ovulation induction only. Assuming a live birth rate of 40% after CC, 55% after addition of IUI and 55% after ovulation induction with gonadotrophins, with an alpha of 5% and a power of 80%, we need to recruit 200 women per arm (800 women in total).

An independent Data and Safety Monitoring Committee has criticized the data of the first 150 women and concluded that a sample size re-estimation should be performed after including 320 patients (i.e. 80 per arm).

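### The primary outcome is named as the birth of a healthy child, but live birth is defined as a pregnancy still ongoing past 24 weeks, which requires neither a delivery nor a living child

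*Protocol article*

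**What the plan says.** The Primary outcome measure section has two sentences that matter here. The first names the outcome: "birth of a healthy child resulting from a pregnancy that was established in the first eight months after randomisation". The second gives a rule: "A live birth is defined as any ongoing pregnancy with a gestation time beyond 24 weeks". No other rule for the primary outcome appears in the article, and no section says what makes a child healthy.

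Other sections use related but different terms:

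- The Abstract and the Interventions section repeat the healthy-child wording.
- The Objective evaluates the regimens in women "that failed to conceive after six ovulatory cycles with CC in terms of singleton live birth".
- The Economic evaluation works "with the costs per singleton pregnancy within eight months after randomisation resulting in live birth as the primary outcome measure".
- The Cost-effectiveness analysis uses cost per live birth and an incremental ratio per additional live birth.
- The Power calculation is built on live birth: "Assuming a live birth rate of 40% after CC, 55% after addition of IUI and 55% after ovulation induction with gonadotrophins".

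On data collection, the Follow up section states: "Women will be contacted by telephone to enquire on the pregnancy, delivery and the health of the child". It adds contact with child health centres or paediatricians when needed. Among the secondary outcomes, miscarriage is a loss "before the 20th week of pregnancy".

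**The concern.** An ongoing pregnancy is not a birth. The sentence that turns the primary outcome into something that can be coded asks only that the pregnancy has passed 24 weeks. It does not ask that the woman has delivered, that the child was alive, or that the child was healthy. It therefore contradicts the sentence before it and the word it sets out to define.

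Two careful analysts could produce different primary results from the same case record forms. One would follow the definition and count pregnancies past 24 weeks. The other would follow the outcome's name and count deliveries of a healthy child. A third, starting from the Objective, would also exclude twins. The live birth rate in the power calculation and the denominator of the cost-effectiveness ratio inherit the ambiguity, so both the clinical and the economic result could be reported under a label that does not match what was counted.

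**Working it through.** **Step 1: classify the same pregnancies under each wording.** Each pregnancy is assumed to have begun within the eight-month window.

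| Course of the pregnancy | Definition sentence | Outcome as named | Objective (singleton live birth, ordinary meaning) |
|---|---|---|---|
| Past 24 weeks, end not ascertained | success | cannot be judged | cannot be judged |
| Past 24 weeks, stillbirth | success | failure | failure |
| Liveborn singleton with health problems | success | failure, if healthy is applied | success |
| Healthy liveborn twins | success | success, no singleton condition stated | failure |
| Loss between 20 and 24 weeks | failure | failure | failure |

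The first two rows follow from the definition sentence alone. The third depends on whether healthy is a separate requirement, which the article does not settle. The fourth shows the singleton mismatch. The fifth is a failure under every wording, but it also falls outside the definition of miscarriage, so it has no loss category of its own.

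**Step 2: the plan's own figure.** The Power calculation gives 40% against 55%, alpha 5%, power 80%, and 200 women per arm. The usual two-sided formula for two proportions, with mean proportion 0.475, is

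n = [1.96 × √(2 × 0.475 × 0.525) + 0.842 × √(0.40 × 0.60 + 0.55 × 0.45)]² / 0.15² ≈ 173 per group,

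or 186 with a continuity correction. The stated 200 is not reproduced; comparing 200 with 200 gives 85.4% power. That is a separate matter. It is shown only as the base for Step 3.

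**Step 3: can the effect of the misclassification be sized?** Let f₁ be the share of pregnancies past 24 weeks that do not end in the intended outcome in the 40% group, and f₂ the same share in the 55% group. The article gives neither, so every value below is an assumption.

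Difference = 55 × (1 − f₂) − 40 × (1 − f₁).

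With equal shares:

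| Share in both groups | Rates | Difference | n per group | Power, 200 vs 200 |
|---|---|---|---|---|
| 1% | 39.6% vs 54.45% | 14.85 points | 177 | 84.8% |
| 2% | 39.2% vs 53.9% | 14.7 points | 180 | 84.1% |
| 5% | 38.0% vs 52.25% | 14.25 points | 191 | 81.9% |
| 10% | 36.0% vs 49.5% | 13.5 points | 210 | 78.1% |

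Equal shares leave the relative risk, which is the planned effect measure, at 55 / 40 = 1.375, because the factor (1 − f) cancels.

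With unequal shares, taking f₁ anywhere from 1% to 4% and f₂ anywhere from 1% to 10%:

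- smallest difference: 55 × 0.90 − 40 × 0.99 = 49.5 − 39.6 = 9.9 points, relative risk 49.5 / 39.6 = 1.25;
- largest difference: 55 × 0.99 − 40 × 0.96 = 54.45 − 38.4 = 16.05 points, relative risk 54.45 / 38.4 = 1.42.

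The range lies on both sides of 15 points. These assumptions therefore fix neither the size nor the direction of the effect.

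**The case against.** The strongest reply is that the definition sentence is a badly worded gestational threshold on a birth outcome. The preceding sentence speaks of a birth, the Follow up section pursues each pregnancy to delivery and asks about the child, and the case record form registers pregnancy outcome. On that reading nobody would code an undelivered pregnancy as a birth. This is a fair guess at the intention, and it means that the data for a correct endpoint should exist. It does not rescue the text. The article is not silent, so this is not a detail left to a fuller document; it states a rule, and the rule gives a wrong answer for a stillbirth after 24 weeks.

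Three stronger readings are tempting, and the document supports none of them:

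- **That the error favours gonadotrophins.** The Discussion does say that gonadotrophins carry a higher risk of multiple gestation, and a reader might infer more failures after 24 weeks in those arms. Nothing in the article links multiple pregnancy to such failures or gives a rate, and the inference says nothing about the IUI comparison.
- **That counting a liveborn child with health problems is an error of the same kind.** Any ordinary live-birth definition counts that child. What the article lacks is a definition of healthy.
- **That losses between 20 and 24 weeks disappear.** Such a loss is still a failure on the primary outcome, and it remains a clinical pregnancy if a heartbeat was registered. It lacks only a named class, and the secondary outcomes are not presented as exhaustive.

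**Conclusion.** The point holds as an internal contradiction in the primary outcome and is wrong as written. Coded literally, a pregnancy that ends in stillbirth after 24 weeks is a success; this follows from the wording and needs no assumption. Two further inconsistencies stand beside it: healthy is undefined, and the singleton condition appears in the Objective and the Economic evaluation but not in the primary outcome.

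The numerical consequence is unknown. If the share of affected pregnancies is small and equal across groups, the loss of power is slight and the relative risk does not change. If the shares differ, the effect could be larger and could go either way. The article gives no basis for choosing among these cases, so no claim of bias towards any arm should be made. The reason to correct the text is that the primary endpoint must have one meaning.

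**What to change.** Replace the definition sentence with: *Live birth is the delivery of at least one living child at or after 24 weeks of gestation*, ascertained from the delivery follow-up already planned. Then:

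1. Report pregnancy ongoing beyond 24 weeks as a separate outcome under that name.
2. Either define healthy by criteria obtainable from the planned telephone and paediatric follow-up, or delete the word.
3. State whether the primary outcome is restricted to singletons.
4. Use the resulting single definition in the Abstract, Objective, Interventions, Primary outcome measure, Economic evaluation, Cost-effectiveness analysis and Power calculation. Changing the primary outcome sentence alone would leave the singleton mismatch in place.
5. As a minor point, assign losses between 20 and 24 weeks to a named outcome class.

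The cost is a few sentences and no new data collection beyond what Follow up already describes. The downside is that the event rate may be marginally lower than under the present wording.

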#### Secondary outcome measures

• Multiple pregnancy, defined as a registered heart beat of at least two fetuses at 12 weeks of gestation.

• Clinical pregnancy, defined as any registered heart beat at sonography.

• Miscarriage, defined as loss of an intra uterine pregnancy (confirmed by ultrasound or histological examination) before the 20th week of pregnancy.

• Ovulation rates, assessed by a biphasic basal temperature curve, midluteal progesterone (> 16 nmol/l), detection of LH surge or sonography.

#### Background and demographic characteristics

To assess whether the treatment groups are balanced, the study populations will be compared for baseline measurements including female age, type of infertility (primary/secondary), duration of infertility, intoxications, body mass index, as well as sperm analysis according to WHO standards.

### Analysis

The analysis of all outcomes is on an intention to treat basis. Couples will be treated within a time horizon of eight months. Two comparisons will be made, one in which CC is compared to gonadotrophins and one in which the addition of IUI is compared to ovulation induction only. Differences in pregnancy outcomes will be expressed in relative risks with corresponding 95% confidence intervals. Birth rates over time will be compared using life tables. Discrete variables (e.g. presence of absence of a complication) will be summarised by frequencies and proportions. Differences between groups with respect to discrete variables will be evaluated by using chi-squared tests. Continuous variables will be assessed for normality and equality of variance between groups. For continuous variables, analysis of variance and/or regression will be used where appropriate.

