**Discussion:**

The trial will provide evidence on the most effective, safest and most cost effective treatment in women with WHO type II anovulation who do not conceive after six ovulatory cycles with CC with a maximum of 150 mg daily for five days. This evidence could imply the need for changing our guidelines, which may cause a shift in large practice variation to evidence based primary treatment for these women.

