### Randomisation

Randomisation is performed by accessing a password protected central internet-based randomisation program and is stratified for hospital. The randomisation list is prepared by an independent statistician. A 2x2 factorial design will be used. This will create four groups:

1) CC plus intercourse

2) CC plus IUI

3) gonadotrophins plus intercourse

4) gonadotrophins plus IUI

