**Figure 1 F1:**
[figure not shown]
Flow chart M-OVIN study.

Ovulation induction, semen preparation and insemination regimens will be done according to hospital specific protocols. Ovulation induction with CC will be started on the third to fifth day of a spontaneous menstrual or progesterone induced bleed, in the same dosage as used in the last ovulatory cycle, with a minimum of 50 mg to a maximum of 150 mg daily, for five days. If ovulation does not occur, the dosage will be increased with steps of 50 mg with a maximum of 150 mg daily in the next cycles. As couples are assumed to have regular intercourse, no specific timing advice will be given. Only if couples have a history of sexual problems they are advised to have regular intercourse, at least three times a week. Ovulation will be documented according to local protocol with either a biphasic temperature curve, or a follicle with a diameter ≥16 mm ;on transvaginal ultrasonography. In case of ovulation women will continue taking the same dose of CC until an end point is reached.

Ovulation induction with gonadotrophins will be started at the second to fifth day of a spontaneous or progesterone induced menstrual bleed according to the established chronic low dose step up regimen. Transvaginal ultrasound will be performed on day three of the cycle or according to local protocol. Women will not be stimulated if they have ovarian cysts >25 mm in mean diameter. The starting dose will be 50 or 75 IU daily. The follicular growth is strictly monitored by transvaginal ultrasound. If more than three dominant follicles (≥18  mm) are present, the cycle will be cancelled. When at least one follicle with a diameter of ≥ 16 mm is present, ovulation is induced by the administration of 5000 IU or 10000 IU of human chorionic gonadotrophin (hCG) followed by timed intercourse.

In case of IUI, semen samples will be processed within one hour of ejaculation by density gradient centrifugation followed by washing with culture medium. Women will be inseminated 36 hours after hCG injection. IUI will be performed once per cycle.

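### The primary objective concerns four regimens, but the clinical analysis names only two factor-level comparisons, and these average IUI and drug contrasts that the protocol describes differently by stratum

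*Protocol article*

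**What the plan says.** The Objective section states: "Our primary objective is to evaluate four treatment regimens in women with WHO type II anovulation". The Abstract's Discussion goes further: "The trial will provide evidence on the most effective, safest and most cost effective treatment". The Randomisation section adds: "A 2x2 factorial design will be used. This will create four groups".

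For the clinical outcomes, the Analysis section then says "Two comparisons will be made, one in which CC is compared to gonadotrophins and one in which the addition of IUI is compared" with ovulation induction only, using relative risks with 95% confidence intervals. The Power calculation section names the same two comparisons. Regimen-level contrasts are found in the Economic evaluation section, which studies the "addition of IUI, use of gonadotrophins or the combination of both as compared to CC alone", and in the Cost-effectiveness analysis section, where incremental ratios are formed against CC alone.

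The Interventions text below Figure 1 describes the components:

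- CC: "As couples are assumed to have regular intercourse, no specific timing advice will be given". No hCG is described for CC plus intercourse.
- Gonadotrophins: ovulation is triggered with "human chorionic gonadotrophin (hCG) followed by timed intercourse".
- IUI, with no distinction by drug: "Women will be inseminated 36 hours after hCG injection".

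The same text leaves ovulation induction and insemination regimens to hospital protocols.

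**The concern.** In a 2x2 factorial trial, each factor-level comparison averages an effect over the two levels of the other factor. Such an average can guide a choice among four regimens if the effect is much the same at both levels. Here the description itself gives a reason to expect a difference. With CC, moving from intercourse to IUI brings timing as well as insemination (and, as written, hCG). With gonadotrophins, timing and hCG are already present in the intercourse arm, so IUI brings insemination only. The drug comparison is uneven in the same way: among intercourse couples it includes timing, among IUI couples it does not. The main Discussion section lists better timing among the ways in which IUI is thought to work, so unequal effects are foreseeable.

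If IUI helps mainly in CC women, the averaged relative risk understates its benefit there and overstates it with gonadotrophins. A guideline that must choose among four regimens could then be misled by two averages, while the economic evaluation uses regimen-level differences for which the described clinical analysis names no matching relative risks.

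**Working it through.** **Inputs.** The Power calculation section gives 40% after CC, 55% with IUI added, 55% with gonadotrophins, alpha 5% (taken as two-sided), power 80% and 200 women per arm. It gives no rate for gonadotrophins plus IUI. Call that rate x and **assume** 55%, 60% or 70%; 70% is the additive value, 55 + 55 − 40.

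**The plan's own figure.** For 40% against 55% with pooled variance under the null:

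n = [1.96·√(2·0.475·0.525) + 0.842·√(0.40·0.60 + 0.55·0.45)]² / 0.15² = 173 per compared group, or 186 with continuity correction.

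The stated 200 per arm does not follow exactly from these inputs; an unstated allowance could explain it (186/0.93 = 200). Power for 40% against 55% is 85% with 200 against 200, and 99% with 400 against 400. The stated size is therefore closer to what an arm-against-arm comparison needs than to what a factorial margin needs.

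**Within-drug and pooled relative risks for IUI, equal arms.**

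- With CC: 0.55/0.40 = 1.375.
- With gonadotrophins: x/0.55.
- Pooled: [(0.55 + x)/2] / [(0.40 + 0.55)/2] = (0.55 + x)/0.95.

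**Interaction on the risk-difference scale.** The interaction is x − 0.55 − 0.55 + 0.40. Its standard error is √{[0.24 + 2(0.2475) + x(1 − x)]/200}, which at x = 55% is √(0.9825/200) = 0.0701.

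| Assumed x | RR of IUI with CC | RR of IUI with gonadotrophins | Pooled RR | Power of margin, 400 vs 400 | Interaction | Power for interaction |
|---|---|---|---|---|---|---|
| 55% | 1.375 | 1.00 | 1.16 | 57% | 15 points | 57% |
| 60% | 1.375 | 1.09 | 1.21 | 81% | 10 points | 30% |
| 70% | 1.375 | 1.27 | 1.32 | 99% | 0 points | – |

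Because the stated rates for adding IUI and for gonadotrophins are equal, the same figures apply to the gonadotrophin relative risk within intercourse (1.375), within IUI (x/0.55) and pooled.

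At x = 55%, 80% power for the interaction needs about 2.8 × 7.0 = 19.6 points. At the other end, a constant relative risk would require x = 0.55 × 1.375 = 75.6%, and the pooled value would then equal both within-drug values.

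**Precision, as 95% half-widths of the risk difference.**

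- Within CC: 1.96·√[(0.24 + 0.2475)/200] = 1.96 × 0.0494 = 9.7 points.
- Margin at x = 70%: 1.96 × ½·√(0.945/200) = 6.7 points.
- Margin at x = 55%: 1.96 × ½·√(0.9825/200) = 6.9 points.

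**The case against.** The strongest reply is that two margins are the standard analysis of a factorial trial. Under randomisation each margin is an unbiased intention-to-treat estimate of the effect averaged over the other factor. That stands. A reader might infer that pooling is invalid unless the effects are equal; this is not so. Unequal effects limit what the average can be used for, not its validity.

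A second reply is that arm-level tables and an interaction estimate may sit in a full protocol or analysis plan that is not shown. This stands in part, so their absence from the article is not itself the point. The point is what the article does fix: a four-regimen objective, two named clinical comparisons, and differing descriptions of intercourse. An interaction test elsewhere would not make the two IUI contrasts alike.

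Third, a reader might infer that regimens are never compared, or that the Objective asks which is best. Neither reading is supported. The economic sections do compare regimens with CC alone, and the Objective says only that regimens are evaluated; the promise of a most effective treatment is in the Abstract.

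Fourth, a reader might infer that women on CC plus intercourse receive no hCG. The text is silent and local protocols apply, so only the timing difference is explicit. Timing may also fairly be seen as part of the IUI strategy. That is a legitimate estimand, but it would still differ between the two drug strata.

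Finally, the size of the distortion depends on an unstated rate and is small at 70%. That stands, and it is why a range is shown.

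**Conclusion.** The point holds in this limited form. The stated objective concerns four regimens, the named clinical comparisons concern two factors, and the described intercourse comparators differ between the drugs. The marginal relative risks are unbiased averages that may describe no single regimen. Under the stated 40/55/55, the pooled relative risk for IUI is 1.16 against 1.375 and 1.00 if gonadotrophins plus IUI reaches 55%, and 1.32 against 1.375 and 1.27 if it reaches 70%.

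These figures assume equal arms of 200, the planning rates and a two-sided 5% level. With that size, interaction power is 57% for 15 points and about 30% for 10, so a non-significant test would be weak evidence of equal effects. The randomised data are not compromised: all four arms exist and can be reported without a design change.

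**What to change.** Keep the two marginal comparisons and prespecify beside them:

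- live birth rates for all four arms;
- the IUI relative risk within CC and within gonadotrophins;
- the gonadotrophin relative risk within intercourse and within IUI;
- the interaction with its 95% confidence interval, on a named scale, since additive rates still give unequal relative risks (1.375 and 1.27 above).

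State that regimen-level conclusions rest on the arm-level estimates, and that a non-significant interaction test is not grounds for reporting margins alone. Reconcile or clarify the hCG and timing text in the Interventions section across the four arms, and describe the IUI contrast in each drug stratum accordingly. This asks for a clear description, not for any particular clinical rule. The sample size re-estimation planned after 320 women is a natural point by which to settle which contrasts the trial is meant to support.

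The cost is some wording and a few table rows. The drawback is precision: within-stratum intervals are about ±9.7 points, against about ±6.7 to ±6.9 for the margins.

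### Hospital and the second randomised factor structure the allocation but do not appear in the stated analysis; bringing them in is a near-free improvement in efficiency, not a repair of validity.

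*Protocol article*

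**What the plan says.** All references are to the Protocol article.

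- **Randomisation:** "Randomisation is performed by accessing a password protected central internet-based randomisation program and is stratified for hospital". The same section adds "A 2x2 factorial design will be used", giving four groups.
- **Analysis, comparisons:** "Two comparisons will be made, one in which CC is compared to gonadotrophins and one in which the addition of IUI is compared" with ovulation induction alone. Both are margins of the factorial.
- **Analysis, effect measure:** "Differences in pregnancy outcomes will be expressed in relative risks with corresponding 95% confidence intervals". Whether these are crude or adjusted is not stated.
- **Analysis, test:** "Differences between groups with respect to discrete variables will be evaluated by using chi-squared tests". Births over time are compared with life tables. Analysis of variance and regression are mentioned for continuous variables only.
- **Interventions (text under Figure 1):** "Ovulation induction, semen preparation and insemination regimens will be done according to hospital specific protocols".

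Hospital and the other randomised factor are not named as strata or covariates for any binary outcome. The number of hospitals and the size of any difference in birth rates between them are not given.

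**The concern.** Stratified randomisation removes between-hospital variation from the treatment contrast, and the factorial crossing does the same for the other factor. A plain chi-squared test does not take credit for this: its variance still contains the variation between strata. If the strata predict live birth, the standard error is too large, intervals are somewhat wide, and the test rejects a true null less often than its nominal 5%.

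There is reason to expect some effect of the strata. Treatment regimens follow local practice, as do the methods for confirming ovulation and tubal patency (Inclusion criteria, Study management). The other randomised factor is assumed in the Power calculation to move the live birth rate from 40% to 55%. At stake is some precision and power that the design has already paid for.

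**Working it through.** **1. The plan's own figure.** For 40% versus 55%, two-sided 5% (sidedness assumed), 80% power, with mean rate 0.475:

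n = [1.960·√(2·0.475·0.525) + 0.842·√(0.40·0.60 + 0.55·0.45)]² / 0.15² = 173 per group, or 186 with continuity correction.

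The stated 200 per arm is above both and gives 85.4% power for one arm against another. Each factorial margin compares 400 with 400, and power for 40% versus 55% is then 99.0%. The stated size is therefore on the safe side and does not create this point, but it limits how much power can be lost.

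**2. Analytic approximation.** Let s be the share of outcome variance explained by the ignored strata, with allocation balanced within them. The crude standard error exceeds the correct one by a factor 1/√(1−s). Then:

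- true alpha = 2·[1 − Φ(1.960/√(1−s))]
- crude power, where the stratified test has 80% = Φ(1.960 + 0.842 − 1.960/√(1−s))

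For the other factor, s follows from the protocol's rates: 0.075² / (0.475·0.525) = 0.0226. For hospital, s is an assumption and is shown over a range.

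| Ignored strata | s | SE excess | True alpha | Crude power (stratified = 80%) |
|---|---|---|---|---|
| none predictive | 0 | 0% | 5.0% | 80.0% |
| hospital 1% | 0.01 | 0.5% | 4.9% | 79.7% |
| hospital 2% | 0.02 | 1.0% | 4.8% | 79.4% |
| other factor only | 0.0226 | 1.1% | 4.7% | 79.4% |
| hospital 5% | 0.05 | 2.6% | 4.4% | 78.5% |
| hospital 10% | 0.10 | 5.4% | 3.9% | 76.9% |
| hospital 5% + other factor | 0.0726 | 3.8% | 4.2% | 77.8% |
| hospital 10% + other factor | 0.1226 | 6.8% | 3.6% | 76.1% |

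**3. Simulation.** Assumptions: 800 women, 20 hospitals of 40, four arms balanced within hospital, other-factor log-odds about 0.6. The crude test is compared with a Cochran-Mantel-Haenszel (CMH) test over hospital by other factor. The tested effect is either the protocol's, ln(0.55/0.45) − ln(0.40/0.60) = 0.606, or a smaller log-odds of 0.4 (about 10 percentage points). The latent intraclass correlation is SD²/(SD² + π²/3).

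| Hospital SD (logit) | Latent ICC | Crude alpha | Power gained by stratifying, 40% vs 55% | Power gained, log-odds 0.4 |
|---|---|---|---|---|
| 0.3 | 0.03 | 4.6% | 0.1 points | 0.5 points |
| 0.6 | 0.10 | 4.1% | 0.4 points | 2.6 points |
| 0.9 | 0.20 | 3.4% | 1.1 points | 5.4 points |

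The stratified test held alpha at about 5%. Repeat runs of 8,000 trials agreed within simulation error: at SD 0.9, crude alpha was 3.3% to 3.5%, and the gain was 1.5 points at the protocol's effect and 5.6 to 6.2 points at log-odds 0.4. With no hospital effect, a repeat run gave alpha 4.7% crude against 4.8% stratified, and power (log-odds 0.4) 78.8% against 79.1%.

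**4. Sensitivity.** With 10, 20 or 40 hospitals and a latent ICC of 0.105, crude alpha was 3.7% to 4.1%, and stratifying gained up to about 3 points of power. That set includes the case where the combined arm also has 55%, a rate the protocol does not state. The marginal contrast is then only (40+55)/2 = 47.5% versus 55%; with 20 hospitals, power was 50.6% crude and 53.4% stratified.

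**The case against.** The strongest objection is that this reads a decision into silence. The article is condensed and a separate analysis plan may specify adjustment. The chi-squared sentence follows an example about complications, and pregnancy outcomes have their own sentence on relative risks.

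Much of this stands. A reader might infer that the relative risks are crude and that the plan has decided to disregard hospital; the text says neither and excludes no adjustment. What remains is that the Analysis section does name its methods: chi-squared for discrete variables, of which live birth is one, and regression for continuous ones. As ordinarily understood, that chi-squared test is unstratified.

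Three further inferences are tempting and unsupported:

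- **That the results would be invalid.** The error is conservative. Under balanced allocation the marginal relative risk is unbiased, and chance imbalance in prognostic factors is random error that the interval already covers.
- **That the trial stands to lose 5 points of power.** This needs both an effect smaller than the protocol's and a hospital SD of 0.9. Local regimens make a hospital effect plausible, but the documents give no figure for it and nothing that supports an ICC of 0.20.
- **That the baseline comparison is a misuse of significance testing.** The section on background characteristics says "To assess whether the treatment groups are balanced, the study populations will be compared for baseline measurements" and names no test. A descriptive table fits that wording.

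**Conclusion.** The point holds as a modest efficiency gain. The direction is certain wherever hospital or the other factor predicts live birth. The size rests on assumptions about the number of hospitals, the between-hospital SD and balance of the four arms within hospitals, none of which the protocol quantifies. Only the contribution of the other factor follows from the protocol's own rates, and alone it takes alpha from 5.0% to 4.7%. At the planned effect and sample size the power at stake is around 1 point or less. It would matter more if the true effect is smaller than planned, or if the sample size re-estimation at 320 women led to a smaller trial. The reason to act is that the change costs almost nothing, not that the present wording is unsafe.

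**What to change.** State in the Analysis section that the primary estimate for each of the two comparisons is a relative risk stratified by, or adjusted for, hospital and the other randomised factor. Two routes are suitable:

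- a Mantel-Haenszel relative risk with a CMH test; or
- a regression that yields an adjusted relative risk.

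Add a pre-specified rule for pooling hospitals with very few women, and keep the crude relative risk as a supportive result. Adjustment for female age and duration of infertility, both already collected, is an optional addition; they were not stratification factors. If a separate analysis plan already provides for this, one aligning sentence is enough.

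The cost is wording and the pooling rule. No further data or recruitment is needed, and in simulation the stratified test was no worse in practice even without a hospital effect. It is best fixed before the sample size re-estimation.
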